##### Data linking

Survey data will be linked across intervention Years 1 and 2 for each Cohort. In order to maintain anonymous management of data, GISD will generate individual codes in the de-identified data. The impact of each year of the intervention will be assessed as well as change after 2 years of implementation. Rarely is the stability of an intervention examined, particularly one that is designed to affect change in school climate. The two-year implementation of the intervention provides a unique opportunity to assess the intervention over a longer period.

##### Dichotomous outcome variates

The outcome measure required is the net average change, i.e. the proportion changing from negative at baseline to positive at follow-up minus the proportion changing from positive at baseline to negative at follow-up. This can be modeled in multinomial form with categories—upward change (from negative for the behavior to positive for the behavior), downward change (the reverse), with no change as reference category—and analyzed using multiple logistic regression for a cluster design by e.g., the GENMOD procedure in SAS.

As a test of the conceptual framework (secondary aim), mediating variables would be included in these analyses (e.g., of school climate on mental health). Change in certain behavioral variables, including composite variables, will be correlated by a multivariate extension of the above techniques to examine the relationship between school climate, mental health, and violence.

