### Sample

#### Schools

We will recruit 20 schools and implement the intervention across three school years (see Table 1). Co-educational elementary schools in Genesee County Intermediate School District (GISD), Michigan will be invited to participate. Schools participating will be similar in terms of proportion of students receiving free/reduced school lunches and approximate size of the school. Prior to the intervention roll-out, all 20 schools will be randomized to intervention or control. The intervention will be implemented in stages. Cohort 1 schools will include 5 intervention and 5 control schools. Cohort 2 will include10 additional schools (5 intervention and 5 control) for a total of 10 intervention and 10 control schools; each school will implement the intervention for two years.

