#### Behavioral outcome analysis

We will undertake comparability of the two arms (intervention and control) will be undertaken, including school size and socio-demographic indicators (e.g., proportion of free/reduced school lunches, proportion of students from various ethnic backgrounds, aggregate reports of income). Our primary analytic strategy uses mixed-effects models with full information maximum likelihood, which uses all available data for point estimation and sandwich estimator for the standard errors.

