##### Quantitative variates (e.g., violence; climate; mental health)

Essentially the same analytic structure as described above for dichotomous variates will be employed, but without the logit link for linear variates (it may be necessary to transform these quantitative variates, depending on their distributions.)

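### The up/down/no-change analysis of behavioural outcomes does not fit the all-data mixed model named as primary, takes no account of baseline status, and yields coefficients that are not the stated net change

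*Protocol article*

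**What the plan says.** All the relevant text is in the protocol article.

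- Under Behavioral outcome analysis: "Our primary analytic strategy uses mixed-effects models with full information maximum likelihood". The sentence adds that this uses all available data for point estimation, with sandwich standard errors.
- Under Dichotomous outcome variates: "The outcome measure required is the net average change", defined as the proportion moving from negative to positive minus the proportion moving the other way. The text continues: "This can be modeled in multinomial form with categories". The categories are upward change and "downward change (the reverse), with no change as reference category". They are to be "analyzed using multiple logistic regression for a cluster design by e.g., the GENMOD procedure in SAS". No baseline term is named, and nothing says how the two contrasts become a net change or which of them is tested.
- Under Quantitative variates, whose heading lists violence, climate and mental health: "Essentially the same analytic structure as described above for dichotomous variates will be employed", without the logit link.
- The Analysis section sets four time points, fall and spring of Years 1 and 2. Data linking says that each year's impact and the change after two years will be assessed.

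**The concern.** The primary aim concerns violence. The article points to two ways of analysing it and does not say how they relate. They use different students, different waves and different effect measures, so they can give different answers.

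The change-category model has two weaknesses of its own. First, it tests odds ratios, whereas the required outcome is a difference of proportions. Second, only students negative at baseline can move up and only students positive at baseline can move down. The reference category nevertheless pools stable negatives with stable positives. The result therefore depends on where each arm started, and with 20 randomised schools the arms may start some way apart by chance.

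**Working it through.** **Inputs from the article.** The net-change definition and the three categories; 10 schools per arm (Schools); 60 students per school, a prior ICC range of .00 to .03 and a planning value of .10 (Between group analyses); four time points (Analysis). The article gives no prevalence, transition rate or numerical result for this analysis, so there is no figure to reproduce. The prevalences, transition rates and correlations below are assumptions.

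**1. Net change.** Let b be baseline prevalence, u the probability of becoming positive if negative, and d the probability of becoming negative if positive. Then up = (1 - b)u and down = bd, so net change = up - down = u - (u + d)b. This equals follow-up prevalence minus baseline prevalence.

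**2. Odds ratios against net change.** Take b = .30 in both arms.

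- Control, u = .15 and d = .45: up .105, down .135, none .760, net -.030.
- Intervention, u = .107 and d = .35: up .075, down .105, none .820, net -.030.
- OR up = (.075/.820)/(.105/.760) = 0.66. OR down = (.105/.820)/(.135/.760) = 0.72. The difference in net change is 0.

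The mismatch also runs the other way. With up/down of .10/.10 against .09/.19, OR up = (.09/.72)/(.10/.80) = 1.00 and OR down = (.19/.72)/(.10/.80) = 2.11, while net change differs by -.10.

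**3. Net change is recoverable.** With A = log(up/none) and B = log(down/none), net change = (e^A - e^B)/(1 + e^A + e^B). In a multinomial logit fitted to simulated data with 20,000 students per arm, the derived arm difference was -0.07665 and the empirical difference was -0.07665.

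**4. Baseline gap with no treatment effect.** Take u = .15 and d = .45 in both arms, so net = .15 - .60b.

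- b = .25: up .1125, down .1125, none .775, net 0.
- b = .35: up .0975, down .1575, none .745, net -.06.
- OR up = (.0975/.745)/(.1125/.775) = 0.90. OR down = (.1575/.745)/(.1125/.775) = 1.46.

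A 10-point gap thus gives a 6-point difference in net change. With u = .10, d = .40 and baselines of 20% and 30%, OR up is 0.91, OR down is 1.56 and the net difference is -.05.

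**5. Size of a chance gap.** SD = sqrt{2p(1 - p)[1 + (m - 1)ICC]/(10m)}, with p = .30 and m = 60. The last column is the SD times .60 from step 4.

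| ICC | Design effect | SD of gap (points) | Shift in net change per SD (points) |
|---|---|---|---|
| 0 | 1 | 2.6 | 1.6 |
| .03 | 2.77 | 4.4 | 2.6 |
| .10 | 6.9 | 6.9 | 4.2 |

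The 10-point gap in step 4 is therefore 3.8, 2.3 and 1.4 SD respectively.

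**6. Scales, if analysed as unadjusted change.** The variance of a baseline-adjusted analysis relative to a change-score analysis is (1 + r)/2, where r is the correlation of school means over time. At r = .5 it is .75, or 25% less variance. Write r = w × (school-level correlation) + (1 - w) × (individual-level correlation), with w = ICC/[ICC + (1 - ICC)/60].

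- ICC .03: w = .65. Correlations .5 and .3 give r = .43 and ratio .715, about 28% less.
- ICC .10: w = .87. Correlations .9 and .7 give r = .874 and ratio .937, about 6% less.

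**7. Data used.** A student seen at only one of the two waves has no change category and drops out, but still contributes to a likelihood-based mixed model. Each change category uses two of the four waves. The article does not separate consent from retention, so this loss cannot be sized from it.

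**The case against.** The strongest reply is that nothing here is a firm contradiction. Only the mixed model is called primary. The multinomial text is permissive: it says the outcome can be modelled that way and offers the software procedure as an example. A condensed article may leave the back-transformation and the covariate list to the analysis plan. That softens the conflict, but it leaves open which analysis tests the violence hypothesis, and a paired change category still cannot use all available data.

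A reader might infer that the multinomial model cannot estimate net change. Step 3 shows that it can, exactly. What is absent is the stated conversion and a test of it. Nor is the first example in step 2 a false positive in every sense: the assumed transitions do differ between arms, and the model reports that. It shows that testing the odds ratios is not testing the required outcome.

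A reader might also infer that ignoring baseline biases the trial. Schools are randomised, so imbalance averages out over randomisations, and a correctly clustered standard error reflects it. The net-change measure is as sensitive to baseline as the odds ratios, so the fault is not in the model alone. The 10-point gap is large at the ICCs the article says were seen before.

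Finally, Table 1 might be set against "Schools participating will be similar in terms of proportion of students receiving free/reduced school lunches". That sentence concerns lunch eligibility and approximate size only. The lunch values of 52% to 97% all meet the 50% eligibility rule, and minority share and proficiency do not bear on it. Adding lunch percentage or cohort as covariates is a preference for the analysis plan and no part of this point.

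**Conclusion.** The point holds in a limited form. The change-category analysis and its extension to scales do not fit the mixed-model strategy named as primary: they need paired data, use two of four waves and do not condition on baseline status. The odds ratios are not the stated net change and can differ from 1 when net change is equal between arms.

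Under the assumed prevalence and transition rates, a one-SD chance baseline gap moves net change by 1.6 points at ICC 0, 2.6 at .03 and 4.2 at .10, with no treatment effect. This is conditional bias and lost precision, not systematic bias. The 6% to 28% variance saving for scales rests on assumed correlations and on reading the quantitative section as unadjusted change, which its wording suggests but does not settle. The article does not support saying that net change cannot be estimated, or that it declares two primary analyses.

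**What to change.** Make the mixed model the single primary analysis for each outcome type: logistic for binary outcomes, linear for scales, with school and student clustering. Use all waves, either with the Fall Year 1 value as a covariate or as an arm-by-wave model that constrains the arms to a common baseline. The constrained form also keeps students who lack a Fall Year 1 value, so it better honours the promise to use all available data. Name the wave contrast that tests the hypothesis.

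Report the arm difference in prevalence from the model's predicted probabilities, averaged over the random effects. With a common baseline this equals the arm difference in net change, by step 1. Keep the up/down table as description, and reword the quantitative section to refer to the mixed model.

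The cost is minor wording and analysis work, with no new data for the survey outcomes. One limit: Table 2 lists no Fall Year 1 measurement for truancy and behavioural referrals, so for those the plan must say what serves as baseline or that there is none.

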##### Quantitative variates (e.g., violence; climate; mental health)

Essentially the same analytic structure as described above for dichotomous variates will be employed, but without the logit link for linear variates (it may be necessary to transform these quantitative variates, depending on their distributions.)

#### Implementation outcomes

We will assess feasibility and potential utility of using implementation facilitation through focus groups. A minimum of two study team members will take detailed field notes during focus group sessions. We will use the field notes to develop a broad understanding of content as it relates to the project’s specific aims and to identify topics of discussion and observation. During this and subsequent steps, we will document initial impressions of topics and themes and their relationships to each other to define the boundaries of specific codes (e.g., the inclusion or exclusion criteria for assigning a specific code; (Miles, Huberman, & Saldaña, 2014) The empirical material from the focus groups will be coded by project team members to condense the data into analyzable units. Segments of text will be assigned codes based on a priori or emergent themes, also known as open coding (Strauss & Corbin, 1998). Codes will also be assigned to describe connections between categories (e.g., barriers and feasibility). Lists of codes developed by each investigator will be matched and integrated into a single codebook. We will use these codes to examine the association between different a priori and emergent categories. Through the process of continually comparing these categories, the different categories will be further condensed into broad themes. We will also evaluate outcomes using descriptive analyses from teacher surveys and a mixed methods approach to develop a comprehensive understand of using Facilitation to deliver the interventions. Results from each data set will be examined side-by-side to explore convergence (i.e., comparing analysis conclusions) to investigate if qualitative and quantitative results concur. We will also investigate how focus group results elaborate on quantitative results (expansion) to deepen our understanding of why and how Facilitation may or feasible for comprehensive school safety in low resource communities (Palinkas et al., 2011).

#### Process evaluation

An intervention of this nature and size requires a comprehensive process evaluation to monitor implementation and sustainability. Specifically, we will focus on barriers and facilitators to implementation. We will investigate barriers and facilitators associated with the context (e.g., implementation climate), innovation (e.g., complexity), providers (e.g., confidence, competence) and recipients (i.e., student needs). We will examine key factors through focus groups with school staff, observations and review of 3-PLT meetings and activities.

#### Cost-benefit analysis

Following findings of reduced violence, we will examine the costs and benefits of the intervention. The program will be compared with the alternative intervention of no program (control). Although the intervention is targeted to reducing violence, it will likely have additional effects; this adds complexity to the analysis. We will focus on benefits associated with reduced violence, based on previously used methodology to obtain costs (Foster & Jones, 2006; Kuklinski, Briney, Hawkins, & Catalano, 2012). This strategy considers the proportion of school violence from national costs estimated for youth violence and related early school separation. School absence costs will also be considered, relative to costs associated with processing school truancy and absences associated with fear of attending school. We will compare these benefits with costs associated with implementing the full program.

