**Methods:**

We develop and test an intervention focused on promoting a positive school climate guided by a school-based 3-person leadership team (3-PLT) using a hybrid Type II design. The 3-PLT includes a School Resource Officer, (SRO), administrator and mental health services professional as a newly appointed climate specialist (CS). The interventions to be delivered include 1) Restorative justice, 2) Mental Health First Aid and 3) Crime Prevention Through Environmental Design. The CS will lead the team and coordinate implementation through a process of interactive problem solving and supports, consistent with the implementation facilitation strategy. We will conduct a cluster randomized controlled trial with staged entry over two school years in Genesee County, Michigan (*n* = 20 elementary schools, with 10 participating per school year). We will use a combination of data sources including data collected by schools (e.g., discipline data), a student survey, and a teacher survey. We will also conduct a process evaluation and assess implementation and sustainability through focus groups with key stakeholders, teachers, and students. Finally, we will conduct a cost-benefit analysis.

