### Primary study aim

The primary study aim is to examine the overall effectiveness of the intervention, including change in violence (e.g., fights, bullying, victimization), over time compared with a control group of students who receive school practice as usual.

### Secondary study aim 1

Employ implementation facilitation from an appointed school climate specialist (CS) to support delivery of a multicomponent, integrated intervention and evaluate feasibility and potential utility to support sustainment.

### Secondary study aim 2

Examine specific mechanisms associated with change in mental health (e.g., anxiety, depression, well-being), including perceptions of school climate as a moderator.

### Secondary study aim 3

Estimate the costs of the intervention and its implementation and conduct a cost-benefit analysis for positive outcomes, such as improve school climate perceptions, associated with participation in the interventions.

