##### Cost estimates

We will estimate the resources required for the intervention and its implementation and estimate the net costs using a resource-based costing approach. We will track activities relevant to site replication or implementation costs, versus intervention development and research costs because only the former would be required of other sites who might adopt the intervention program (Hurley & Matthews, 2007; Neumann, Sanders, Russell, Siegel, & Ganiats, 2016). Specifically, we consider implementation costs to be those costs associated with replication that would be required by those adopting the program (Neumann et al., 2016). This would include components of the intervention that require tailoring for replication, recruitment or promotion costs to engage practitioners and participants, and training, supplies and labor costs for evaluation as indicated (Ritzwoller, Sukhanova, Gaglio, & Glasgow, 2009).

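### The cost-benefit analysis is made to follow an undefined finding that violence fell, while the abstract and Secondary study aim 3 promise it without that condition

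*Protocol article*

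**What the plan says.** Four places in the protocol article bear on this.

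- **Abstract, Methods:** "Finally, we will conduct a cost-benefit analysis". No condition is attached.
- **Secondary study aim 3:** the aim reads "Estimate the costs of the intervention and its implementation and conduct a cost-benefit analysis for positive outcomes, such as improve school climate perceptions". There is no violence condition, and the example of a benefit is school climate.
- **Cost estimates:** "We will estimate the resources required for the intervention and its implementation and estimate the net costs using a resource-based costing approach". This does not depend on any result, and Table 2 has costs tracked monthly.
- **Cost-benefit analysis:** "Following findings of reduced violence, we will examine the costs and benefits of the intervention". The section continues: "We will focus on benefits associated with reduced violence, based on previously used methodology to obtain costs". It adds a second component: "School absence costs will also be considered, relative to costs associated with processing school truancy and absences associated with fear of attending school". It does not say what happens if violence is unchanged or higher, and it does not put a value on climate perceptions.

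**The concern.** The Cost-benefit analysis section starts from a result, not from a stage of work such as completion of the outcome analysis. The estimate that would open the economic analysis is also its main input. Two consequences follow if the condition is applied.

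First, when violence does not fall, the comparison of benefits with costs is not reported. A district deciding whether to fund a climate specialist post has a strong interest in the answer in exactly that case.

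Second, an effect estimate that is carried forward when favourable and dropped otherwise overstates the true effect on average.

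The trigger is also open. Table 2 lists aggression, victimization and bullying under the primary aim, and the section does not say which of these must fall, or whether a favourable sign is enough or significance is needed. That leaves the choice to be made after the results are seen.

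**Working it through.** **Inputs**
- 20 schools, 10 per arm: Sample, Schools.
- 60 students per school, planning ICC .10, detectable d = .27, power above .80: Power analyses, Between group analyses.
- ICCs reported for the outcomes, .00 to .03: same section.
- Two-sided .05 for the between-group test is an assumption. The article gives .05 only for the structural equation power calculation.

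**Standard error of d** for one unadjusted comparison:

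SE = sqrt(4 × (ICC + (1 − ICC)/60) / 20)

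- ICC .03: sqrt(0.2 × (.03 + .97/60)) = sqrt(.009233) = .0961
- ICC .10: sqrt(0.2 × (.10 + .90/60)) = sqrt(.0230) = .1517

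**The plan's own figure.** The cost-benefit section gives no number. The nearest is the detectable effect, (1.960 + 0.842) × SE:
- ICC .03: 2.802 × .0961 = .269
- ICC .10: 2.802 × .1517 = .425

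So .27 is reproduced at the top of the reported ICC range and not at the stated .10, where power at d = .27 is about 43%. That is a separate matter. Here it is the reason for carrying both ICCs.

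**Expected effect, given that the analysis is run.** With the trigger d-hat > c × SE and a = c − d/SE:

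E[d-hat | run] = d + SE × φ(a) / (1 − Φ(a))

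where c = 1.960 for a significant reduction and c = 0 for any favourable estimate. At true d = .27, d/SE is 2.810 (ICC .03) or 1.780 (ICC .10).

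| Trigger | ICC | a | Probability of running | Expected d-hat if run | Ratio to .27 |
|---|---|---|---|---|---|
| Significant | .03 | −0.850 | .802 | .303 | 1.12 |
| Significant | .10 | 0.180 | .429 | .409 | 1.51 |
| Favourable sign | .03 | −2.810 | .998 | .271 | 1.00 |
| Favourable sign | .10 | −1.780 | .962 | .283 | 1.05 |

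A simulation of 2,000,000 draws gave 1.123 and 1.515 for the two significance rows, and 1.00 at both ICCs when no selection was applied.

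**How often the comparison would be missing.** This is one minus the probability of running. Under a significance trigger it is about 20% (ICC .03) or 57% (ICC .10) of trials in which the true effect is .27. Under a favourable-sign trigger it is 0.2% or 3.8%.

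**Limits.** The planned analysis is a mixed-effects model over four time points, so these standard errors are approximate. The ratio applies to the violence effect and not to the whole benefit-cost ratio, which also counts absence costs and divides by programme costs.

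**The case against.** The other side has a good deal of substance, and several stronger readings that a reader might infer do not survive it.

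- *The analysis is run only if violence falls.* The word *only* is not in the text, and the abstract and Aim 3 promise the analysis freely. The documents support an inconsistency between sections, not a settled rule.
- *Aim 3 would get no answer after a null result.* Its costing half would still be delivered, because the Cost estimates section and Table 2 do not depend on the outcome. What is at risk is the benefit comparison.
- *The analysis could never show that the programme is not worth its cost.* A real reduction in violence can be worth less than the programme costs, so a net loss remains possible once the condition is met.
- *The published figure would be wrong and the fix would correct it.* In a trial that does find a reduction, the effect estimate is the same with or without the condition. The bias is one of expectation over trials. The fix adds the missing results and does not alter that point estimate.
- *The inflation is severe.* A ratio of 1.51 needs both a significance trigger and an ICC of .10, against a reported range of .00 to .03. Ratios of 2.40 (ICC .03) and 3.69 (ICC .10) under a significance trigger need a true d of .10, which is not in the documents.
- *Aim 3 restricts the analysis to results that turned out well.* Its wording, "conduct a cost-benefit analysis for positive outcomes, such as improve school climate perceptions, associated with participation in the interventions", can equally mean desirable kinds of outcome, with climate as one example.

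It is also fair to say that the method for carrying uncertainty into net benefit usually belongs in an analysis plan, so its absence from an article is no fault.

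These points limit the size and the wording of the concern. They do not remove the conditional opening of the section or its conflict with the abstract and Aim 3.

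**Conclusion.** The point holds as an inconsistency with a consequence. One section makes the cost-benefit analysis depend on an undefined favourable violence result, and two other places promise it without that dependence. If the dependence is applied, a null or adverse result leaves the benefit half of Aim 3 unreported, and the violence effect used is biased upwards in expectation.

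At the planning effect, the bias runs from negligible (favourable-sign trigger) through modest (significance trigger, ICC .03) to about half as much again (significance trigger, ICC .10). This rests on a two-sided .05 test, a single unadjusted comparison of 60 students per school, and a trigger that the article leaves undefined. Unit costs and programme costs are not affected.

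This concerns a secondary aim and touches no conclusion on effectiveness. It should still be corrected, because an analysis plan that followed the section as written would inherit the condition.

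**What to change.** In the Cost-benefit analysis section, delete the opening condition and state that the analysis is run whatever the violence result. Use the estimated violence effect, whatever its sign, and carry its uncertainty through to an interval for net benefit.

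Reconcile Secondary study aim 3 with that section on which benefits are valued. Either say how climate perceptions enter the valuation, or name violence and absence in the aim.

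The cost is a little more analysis work, since the cost data are collected in any case. The downside is that the net-benefit interval may include a loss, and the report would have to say so.
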